## Abstract

**Background:**

Aniseikonia represents a potential barrier to neuroplasticity which may limit visual outcomes in children with anisometropic amblyopia. Full correction of refractive error is the first step in standard amblyopia treatment, which corrects for image focus but neglects image size differences.

**Methods:**

The MAGNIFY study is a double-masked, randomised clinical trial investigating the effectiveness of aniseikonia correcting lenses in children at first diagnosis of significant anisometropia. We hypothesis that aniseikonia correction lenses will improve image clarity and reduce the retinal size differences producing better visual acuity and stereoacuity improvements after 15 weeks of optical treatment for children with anisometropia. Eligible children will be randomly allocated to the treatment group (aniseikonia-correcting spectacle lenses) or control group (standard spectacle lenses). Visual acuity and binocular functions will be assessed every 5 weeks during the 15-week optical treatment phase according to standard amblyopia treatment protocol.

**Discussion:**

It is possible that correcting aniseikonia along with anisometropia at first diagnosis will promote binocularity as well as increase spectacle adherence by reducing visual discomfort, improving optical treatment outcomes. This could then reduce the need for additional amblyopia treatment such as patching or atropine, reducing the burden on hospital eye departments and potentially improving visual outcomes for children with amblyopia.

**Trial registration:**

Australian New Zealand Clinical Trials Registry (ANZCTR) ACTRN12620000061932. Registered on 24 January 2020. Protocol 15th November 2019, version one.

**Supplementary Information:**

The online version contains supplementary material available at 10.1186/s13063-022-06159-2.

## Background and rationale

Amblyopia is a developmental disorder of vision that affects approximately 3–5% of the population resulting in bilateral and unilateral visual impairment. Unilateral amblyopia arises from unequal input during early visual development commonly caused by misalignment of the eyes (strabismus), large differences in refractive error between eyes (anisometropia) or a disruption of the visual axis (form deprivation). About two thirds of children with amblyopia have anisometropia alone or in combination with strabismus [1–3]. Refractive correction alone (“optical treatment”) is the first-line treatment for amblyopia in children [4, 5], and this can successfully resolve amblyopia (interocular difference of ≤ 1 line) in about 30% of children [6, 7]. The remaining 70% of children usually undergo occlusion or atropine penalisation therapy to further improve vision in the amblyopic eye.

Anisometropia is usually caused by the two eyes having different axial lengths or by the refractive components of the eyes (cornea, lens) being different in shape. Based on optical theory, these differences between eyes can cause the retinal images to be of different size [8–10], a phenomenon known as aniseikonia. Aniseikonia can also be induced optically by spectacle lenses placed in front of the eye, as the power of the lens has an effect on both the clarity and size of the retinal image [11]. This means that patients with anisometropia are likely to experience aniseikonia, and that spectacle corrections for their refractive error can sometimes worsen the aniseikonia [12]

In adults, induced aniseikonia can interfere with binocular functions like stereoacuity and cause visual discomfort [13]. However, in children with anisometropia, the current standard clinical prescribing guidelines do not account for image size differences. Many clinicians usually prescribe standard spectacle lenses that fully correct anisometropia and assume that children will adapt to aniseikonia without any detrimental effect on their binocular vision or visual gains during optical adaptation. Theoretically, significant aniseikonia may also hinder stereoacuity in children, potentially limiting treatment effectiveness. Aniseikonia is potentially responsible for the plateauing of vision often found during standard treatment protocols [14, 15] and the reduced stereoacuity [16] which often results.

Aniseikonia can be corrected by altering the base curve, thickness, and refractive index of spectacle lenses to alter its magnification effects. This can be done in such a way to reduce the image size difference between the two eyes. A number of companies currently supply lenses designed to correct aniseikonia, and these iseikonic lenses are often used for patients with anisometropia (with or without amblyopia). However, there has not been a direct comparison study investigating the effectiveness of these aniseikonia-correcting lenses compared to standard spectacle lenses for treatment of anisometropic amblyopia in children.

## Objectives and hypothesis

### Research hypothesis

Aniseikonia correction lenses will improve image clarity and reduce the retinal size differences producing better visual acuity and stereoacuity improvements after 15 weeks of optical treatment for children with anisometropia.

### Study objectives

#### Primary objective

The primary objective is as follows: to assess the change in visual acuity of the amblyopic eye from baseline after 15 weeks of wearing spectacle lenses that equalise retinal image size as well as retinal image clarity in children with anisometropic amblyopia. We hypothesise that correction of aniseikonia will help binocularity, producing greater visual acuity and stereoacuity improvements after 15 weeks of optical treatment.

#### Secondary objectives

The secondary objectives are as follows: change from baseline in stereoacuity after 15 weeks of spectacle wear. Improvement in stereoacuity is a key secondary objective as correcting aniseikonia may reduce the binocular mismatch of image size, allowing improved binocular combination and stereopsis.

Objective adherence with optical correction will also be assessed. Iseikonic corrections may improve spectacle comfort in those with anisometropia, which may then lead to better spectacle adherence and in turn, better visual outcomes.

## Methods

### Study design

The MAGNIFY study is a randomised clinical trial, designed as a superiority study with investigator and participant masking to treatment allocation, investigating the visual acuity and stereoacuity outcomes of incorporating aniseikonic correction (lenses that equalises image size and image clarity) into spectacles for children with anisometropic amblyopia compared to standard lenses which correct for image clarity only. This protocol was developed according to SPIRIT guidelines [17].

### Setting

Data will be collected at the Optometry Clinic at the School of Optometry and Vision Science, the University of Auckland, Grafton Campus, Auckland.

### Participants and recruitment

Potential participants will be identified through referrals from paediatric ophthalmologists and experienced paediatric optometry clinics which follow the same prescribing guidelines for children. Initial diagnosis of anisometropia will be made following a comprehensive eye examination including binocular function testing and a cycloplegic refraction. Potentially suitable participants/parents/guardians will be given a copy of the participant information sheet by their eye care provider. With consent from the patient/parents/guardians, the eye care provider will send the contact information to a member of the study team who will contact the participant and invite them to a registration visit to assess eligibility. Parents/guardians of potential participants are also able to contact the study team directly and a copy of the participant information sheet will be sent either electronically or by mail and consent will be sought to contact their eye provider for release of the relevant clinical information. The registration visit will be used for the consenting procedure and for assessing eligibility (Appendix 2).

Recruitment began on 27 February 2020 and is scheduled to end 11 October 2022.

### Eligibility

The following inclusion criteria exist for this trial:
Children aged 4 to < 8 years oldAnisometropia that has not yet been treated by spectacles or occlusionUncorrected visual acuity in the worst eye of 6/12 (0.30 logMAR) or worse, with an interocular difference of 2 lines or more. Sound eye must be 6/7.5 (0.10 logMAR) or better, with an interocular difference of 2 lines or moreAnisometropia ≥ 1.50 DS difference in spherical equivalent between eyes as determined by cycloplegic refractionAstigmatism ≤ 3.00 DCNo manifest strabismus at near or distance on cover testHealthy eyesWilling and able to wear spectacles full-time

The exclusion criteria are as follows:
Myopia exceeding -6.00 DS in spherical equivalentOcular pathology such as a congenital cataract (aphakia/pseudophakia), retinopathy of prematurity, keratoconusPrevious eye surgery of any kindAny known neurological conditions that could potentially affect visionContact lens wear

### Optical treatment

Optical correction is prescribed based on a cycloplegic refraction that is not more than six months old. The correction will be prescribed using criteria designed by the Paediatric Eye Disease Investigator Group [18] and must be as follows: *Hypermetropia—*not under-corrected by more than + 1.50D spherical equivalent and the reduction in plus sphere must be identical between the two eyes. *Anisometropia—*full correction of the anisometropic difference. *Astigmatism—*full cylinder power prescribed. *Myopia—*full correction of myopia. If the participant does not have a copy of a recent (< 6 months old) cycloplegic refraction from their eye care provider, they will be asked to undergo a comprehensive eye examination including a cycloplegic refraction at the University of Auckland Optometry clinic. This will be used to confirm eligibility prior to being enrolled into the study.

### Variable definitions

#### Visual acuity

Amblyopia impairs a broad range of visual functions in the affected eye including visual acuity [19], contrast sensitivity [20] and motion perception [21, 22]. As visual acuity is the gold standard measure of visual function in clinical settings, a widely accepted clinical definition of amblyopia is a difference in best corrected visual acuity between the two eyes of 0.20 log units in the presence of an amblyogenic factor and the absence of any ocular or optic nerve pathology [19]. The amblyogenic factor of interest in this study is anisometropia of ≥ 1.50 DS difference in spherical equivalent. Distance visual acuity (VA) measures are collected separately for OD (RE) and OS (LE). Distance visual acuity will be measured using the highly standardised HOTV protocol adopted by the Amblyopia Treatment Study group and recorded as logMAR units [23].

#### Stereopsis

Amblyopia is commonly associated with impaired stereoscopic depth perception under ordinary (binocular) viewing conditions [24]. Stereopsis will be measured using the clinically well-established Randot Preschool test (Stereo Optical Co. Inc., Chicago, IL, USA) [25]. Stereopsis will be analysed as a categorical outcome: “Improved” or “Not improved” at each follow-up compared to the baseline visit. The participant’s stereopsis threshold is considered to have improved compared to baseline if there is a reduction in log10 (Threshold) value of 0.60 (2-octaves) or more [26] or if the participant’s result changes from Nil Stereo to a measurable threshold. Stereopsis is considered to have worsened compared to baseline if there is an increase in log10 (Threshold) of 0.60 or more or if the participant’s result changes from a measurable threshold to Nil Stereo.

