### Sample size

A sample size of 50 patients (25 per arm) will provide 95% power at *p* = 0.05 to detect a minimal clinically important difference of 0.20 log units improvement in visual acuity as tested on the EVA test [41, 42] at 15 weeks, assuming a standard deviation of 0.17 [43]. This sample size allows for an overall loss-to-follow-up of 15% [44] (calculated using GraphPad Sat Mate 2.0).

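### Stereopsis, the key secondary outcome, is analysed only as improved or not improved at a four-fold step; a baseline-adjusted ordered analysis would use the same data better and keep worsening visible

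*Protocol article*

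**What the plan says.** The Secondary objectives section of the protocol article gives stereopsis special standing: "Improvement in stereoacuity is a key secondary objective". The research hypothesis names it beside visual acuity, and the Secondary outcomes list has it as change from baseline at 5, 10 and 15 weeks.

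The Stereopsis section sets the form of the analysis: "Stereopsis will be analysed as a categorical outcome: “Improved” or “Not improved” at each follow-up compared to the baseline visit". There are two routes to 'Improved':

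- a fall in threshold of the stated size, "if there is a reduction in log10 (Threshold) value of 0.60 (2-octaves) or more", a step for which the protocol cites a source;
- a gain of measurable stereopsis, "if the participant’s result changes from Nil Stereo to a measurable threshold".

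A third state is then defined: "Stereopsis is considered to have worsened compared to baseline if there is an increase in log10 (Threshold) of 0.60 or more", or a move from measurable to nil. The two-level outcome has no category for it.

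On the instrument, the section says "Stereopsis will be measured using the clinically well-established Randot Preschool test". The article does not give its levels or its finest disparity. The Eligibility section sets no limit on stereopsis. The Sample size section concerns acuity only, and no power is claimed for stereopsis.

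**The concern.** The test gives a graded threshold, but the planned between-group comparison uses one cut of it. Three things follow from the text:

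- A gain just short of 0.60 log, no change, and a loss all count as 'Not improved'. A treatment that helped some children and harmed others would be judged only on the gains.
- A four-fold gain is impossible for a child who starts within a factor of four of the finest level. Eligibility does not keep such children out.
- Cutting a graded measure costs power, in a trial whose size was chosen for a different outcome.

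At stake is how clear an answer the trial can give on stereoacuity, the outcome closest to the proposed binocular mechanism.

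**Working it through.** **1. The plan's own sample size (acuity).** Inputs from the Sample size section: difference 0.20, SD 0.17, 95% power, 15% loss. The 5% two-sided level is from the Data analysis section.

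- Normal approximation: n per arm = 2 × (1.960 + 1.645)² × (0.17/0.20)² = 18.8, so 19. The t-test version gives 19.8, so 20.
- Allowing for loss: 20/0.85 = 23.5, so 24 per arm, or 48 in total. The stated 50 is consistent with this.
- Evaluable children: 25 × 0.85 = 21.25, so about 21 per arm. With 21, power for acuity is 96%.

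This says nothing about stereopsis.

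**2. The floor.** Two octaves is log10(4) = 0.602, and 10^0.60 = 3.98. For any finest level F, a child with a measurable baseline below about 4F cannot be 'Improved'. F is not given. For assumed values of 20, 40 and 60 arcsec, the limit is about 80, 160 and 240 arcsec.

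**3. Information kept by one cut.** Under a normal model for the change, the efficiency of the split relative to the unsplit measure is φ(z_p)² / [p(1 − p)], where p is the proportion improved.

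| p improved | Efficiency | Loss |
|---|---|---|
| 50% | 0.64 | 36% |
| 30% | 0.58 | 42% |
| 21% | 0.50 | 50% |
| 20% | 0.49 | 51% |
| 10% | 0.34 | 66% |

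The table is symmetric about 50%. The loss is therefore 36–50% for rates between about 21% and 79%, and exceeds half only outside that range. No expected rate is stated.

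**4. Power of the two-level comparison, 21 per arm.** Two-proportion normal approximation; the rates are assumptions.

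- 30% v 60%: pooled p = 0.45. Null SE = √(2 × 0.45 × 0.55/21) = 0.1535 and alternative SE = √((0.21 + 0.24)/21) = 0.1464. Then (0.30 − 1.96 × 0.1535)/0.1464 ≈ −0.01, so power is 50%.
- 30% v 50%: the same steps give 26%.
- For 80% power, a control rate of 30% needs about 72% in the treatment arm; a control rate of 10% needs about 48%.

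**5. Two-level rule against an ordered analysis.** Simulation with 21 per arm. Assumed: levels nil/800/400/200/100/60/40 arcsec, baseline mean 2.3–2.9 log10 with SD 0.45, SD of change 0.35. The ordered analysis is rank ANCOVA on week-15 stereopsis, with nil worst, adjusted for baseline.

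| True shift | Two-level rule | Rank ANCOVA |
|---|---|---|
| 0.3 log | 38–45% | 59–65% |
| 0.4 log | 55–66% | 82–87% |

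Type I error is near 5% for both. Pairing the ends of these ranges, the implied relative efficiency is [(1.96 + z_binary)/(1.96 + z_rank)]², which is 0.53–0.61 and agrees with step 3. About 2–25% of simulated children start too near the assumed floor to improve by the rule, depending on the baseline mean.

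**6. The gain depends on the covariate.** In the same model, ranking week-15 stereopsis with no baseline adjustment gives about 35% power at 0.3 log and 55% at 0.4 log, no better than the two-level rule.

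**The case against.** The case for leaving the plan alone has real weight.

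- **The cut has a source.** The 0.60 step carries a citation, which cannot be inspected here. This supports it as a threshold for change in one child. It does not make it the only or best comparison between groups.
- **Nil Stereo has no log value.** A plain continuous analysis is not available, and a responder rule is one recognised way to keep these children in. An ordered analysis with nil ranked worst keeps them too. It also credits a move from nil to the coarsest level, so that feature is no argument against the two-level rule in particular.
- **Worsening is not hidden from the report.** A reader might infer that it would never be seen. The Data analysis section summarises categorical variables by group as frequencies and percentages, so a three-row table is open to the sponsor. What remains is that the two-level comparison ignores the third state.
- **The loss is not most of the information.** That stronger reading needs fewer than about 21% or more than about 79% to improve, and the protocol supports neither. An efficiency of roughly 0.5–0.6 is a substantial loss, but usually not more than half.
- **The floor may matter little.** The test levels and baseline distribution are not given, so the share of children affected could be trivial or serious.
- **No claim is broken.** Stereopsis is secondary, no power is promised for it, and the two-level test holds its type I error. An unseen analysis plan could add an ordered analysis, although the protocol text as written fixes the two-level form.

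**Conclusion.** The point holds as a weakness in the analysis of a key secondary outcome, not as an error. Three parts rest on the text and arithmetic alone: the outcome has two levels, worsened children are counted with unchanged ones, and a measurable baseline below about four times the finest level cannot become 'Improved'.

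The size rests on assumptions. The 36–50% information loss needs a normal model and 21–79% improving. The power gap of about 20 points or more (38–45% against 59–65% at 0.3 log, 55–66% against 82–87% at 0.4 log) needs the assumed test levels, SDs and 21 evaluable children per arm; other inputs would move these figures.

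A reader might go further and conclude that the trial will return no useful answer on stereopsis. The protocol does not support that, because it gives no expected response rates and no variability for stereopsis. The acuity sample size reproduces and the primary outcome is unaffected.

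**What to change.** In the Stereopsis section, make the main between-group analysis of week-15 stereopsis an ordered one, with Nil Stereo ranked worst, by rank ANCOVA or proportional odds. Adjust for the Randot Preschool result at the baseline visit, which the schedule of tests plans for every child. Do not adjust for registration stereopsis: under the Registration and enrolment visit section and the notes to Table 1 it may come from the referrer, so neither test nor date need be uniform, and with a weakly correlated covariate the power gain disappears (step 6).

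Keep the cited 0.60 log rule as a supporting result, and report improved, unchanged and worsened by arm.

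The cost is wording only: no new data, visits or children. The downside is that an odds ratio or rank difference is slightly harder to state than a percentage, though the percentage is still reported. One limit remains: baseline is measured in the study spectacles, so an immediate effect of the lenses sits inside the baseline value. That is equally true of the current rule, and this change does not alter it.

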#### Subjective aniseikonia

Aniseikonia is likely to be present in those with anisometropic amblyopia [27, 28]. The difference in images sizes could potentially hinder binocular vision. Currently, estimations [29, 30] or empirical calculations [31, 32] are used due to presumed difficulties in measuring subjective aniseikonia, especially in children. Estimations and empirical calculations, however, do not take into account the retinal and cortical adaptations that may occur and therefore accurate measurement of subjective aniseikonia is important to determine the amount of image size difference individually experienced. Subjective aniseikonia is difficult to measure in adults and children, and currently, there is no gold standard test available, and no tests are specifically designed for use in children. A previous study successfully used the Aniseikonia Inspector Version 3 [33] in school-aged children (5 to 13 years old). This current study uses two validated and commercially available tests: the Aniseikonia Inspector Version 3 (Optical Diagnostics, Culemborg, The Netherlands) and the New Aniseikonia (Awaya) Tests (Good-Lite Company, Tokyo, Japan) [34]. These tests will be used to examine testability in pre-school (4– < 8 years old) children in the presence of anisometropic amblyopia.

#### Spectacle adherence

Spectacle adherence is correlated with visual improvements during optical treatment of amblyopia. A wide range of inter-individual variability, with a potential dose-response relationship between visual improvements and hours of spectacle wear, has been previously shown [35]. Currently, adherence with spectacle wear is only assessed indirectly and subjectively via parental reporting [36, 37], which is generally expected to overestimate adherence. This study will include an optional custom-built objective monitoring device (SpecsOn monitor) [38] to monitor spectacle adherence alongside a daily spectacle wear diary for the first 5 weeks. Additional consent for the SpecsOn monitor will be provided on the consent form at the enrolment visit (Appendix 1). The SpecsOn monitor is a small device externally mounted on the spectacle arm and incorporates two temperature sensors. One sensor, directed at the wearer’s temple, measures skin temperature using an infrared detector, the other sensor measures the device’s temperature as an estimate of the ambient temperature. Temperature measurements are taken at 5-min intervals and written to non-volatile memory. Comparisons of the two temperature measurements can be used to determine if spectacles are being worn. The SpecsOn device will be removed after a minimum of 5 weeks, and the glasses wear diary will be continued for the full 15-week duration. As not all participants will opt to wear the SpecsOn monitor, the glasses wear diary will be the main source for adherence monitoring data. Spectacle wear compliance will be based on the total time the participants wore their glasses as recorded in the participants daily wear diary. Diary recording will be encouraged at every study visit.
A participant is considered compliant if they have worn their glasses for ≥ 75% of their awake time. Awake time is estimated by parents and recorded at the registration visit.

